### Statistical Methods

A clinically relevant difference in MxA levels will be compared between cases with viral and bacterial clinical CAP as well as between cases with viral clinical CAP and controls using appropriate statistical methods according to the number and distribution of data points. Sensitivity and specificity for different respiratory viruses with mariPOC respi and the novel RPA-based test will be calculated as compared with real-time PCR. The difference in asthma prevalence and the difference in the number of hospital-requiring respiratory infections between cases and controls as well as between cases and the general child population will be assessed after 3, 7, and (if deemed necessary) 10 years. Data will be presented with 95% CI, and a *P* value of <.05 will be considered significant.

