### Long-Term Complications of Community-Acquired Pneumonia

Studies on the long-term outcomes of radiologically confirmed bacterial CAP have indicated that the disease is associated with later development of asthma and decreased lung function [40,41]. However, most of these studies have followed children who were born more than two decades ago, and the risk might therefore not generalize to a modern setting, given the reported shift in etiology of pediatric CAP [42]. Hence, there is a need for new studies of long-term complications from pediatric CAP, such as the development of asthma and the risk for future respiratory infections.

In summary, there is a need for (1) assessing the diagnostic accuracy of MxA as a biomarker for viral childhood CAP; (2) new studies on clinical CAP etiology in children; (3) evaluating the antigen-based point-of-care test mariPOC; (4) evaluating a novel RPA-based point-of-care test developed at SciLifeLab; and (V) assessing long-term complications from CAP, including the risk of developing asthma and the risk for future respiratory infections.

The overarching aim of the Trial of Respiratory infections in children for ENhanced Diagnostics (TREND) study is to improve the differential diagnosis of bacterial and viral etiologies in children aged below 5 years with clinical CAP. The specific objectives of the study are as follows:

the diagnostic accuracy of MxA for viral CAP in childrenetiology of children with CAPsensitivity and specificity for the mariPOC respi test for the detection of respiratory virusessensitivity and specificity for a novel RPA-based point-of-care test for the detection of respiratory viruseslong-term complications in children with CAP.

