### Study Size and Power Calculation

A total of 300 cases and 120 controls are estimated to be included in the TREND study. For the sample size calculation, we focused on the assessment of MxA levels in cases with viral CAP as compared with cases with bacterial CAP/controls (study I). Overall, 2 power calculations were made, 1 for viral CAP versus bacterial CAP and 1 for viral CAP versus controls. The following assumptions were made: (1) A difference in MxA level of 500 µg/l between the groups was considered clinically relevant. (2) A standard deviation of 1000 and 300 was assumed in cases with viral CAP and bacterial CAP/controls, respectively, based on previous studies on MxA [13,14]. Using an alpha level of .05 (2 sided) at an 80% power, with an additional 20% to account for nonparametric testing and multivariate analyses, 42 children in each group (viral CAP, bacterial CAP, and controls) would be needed. To ensure that enough of the included cases would fulfill the study definitions for viral and bacterial CAP, the proportion of children with viral and bacterial CAP (TREND definition) was calculated in our previous study that assessed Swedish children with x-ray–verified CAP [47]. By doing this, the prevalence of viral and bacterial CAP was estimated at 45% and 14%, respectively. Hence, 300 cases and 42 controls would be needed to ensure sufficient collection of cases with viral and bacterial CAP, respectively. We also would like to compare viral CAP cases with controls testing positive for 1 or more viruses by PCR. In our previous study, 35.4% of asymptomatic children tested positive for 1 or more viruses. Hence, to include a sufficient number of virus-positive controls, we aim at including 300 cases and 120 controls in the TREND study.

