## Discussion

### Principal Findings

The TREND study aims to improve the differential diagnosis of bacterial and viral etiology in children aged below 5 years with clinical CAP presenting at an emergency unit in a tertiary pediatric hospital in Sweden. This is the first study of children with clinical CAP that evaluates the diagnostic accuracy of MxA as a biomarker for viral CAP. Previous studies on MxA have shown promising results on the role of MxA as a biomarker for viral infection but have been smaller in size [14] or have included more heterogeneous groups of study subjects [13,15,16]. The TREND study aims to add further information on the role of MxA as a marker to improve the interpretation of viral PCR positivity and to differentiate between viral and bacterial infections with a specific focus on children with CAP. Further aims are to validate the findings from recent pediatric CAP etiology studies, including the EPIC and PERCH studies, as well as to assess the long-term complications of pediatric CAP [21-24].

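### Objective 1 is the diagnostic accuracy of MxA, but the only MxA analysis stated, and the whole sample size, concern a difference in MxA levels, which does not determine accuracy

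*Protocol article*

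**What the plan says.** The Introduction, under Long-Term Complications of Community-Acquired Pneumonia, gives as its first need "assessing the diagnostic accuracy of MxA as a biomarker for viral childhood CAP", and the list of specific objectives that follows also begins with the accuracy of MxA. In the Discussion, Principal Findings describes TREND as the first study of its kind that "evaluates the diagnostic accuracy of MxA as a biomarker for viral CAP".

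Statistical Methods gives one analysis for MxA: "A clinically relevant difference in MxA levels will be compared between cases with viral and bacterial clinical CAP", and likewise between viral cases and controls, with the method chosen according to the number and distribution of the data. The next sentence turns to accuracy, but for the other two tests: "Sensitivity and specificity for different respiratory viruses with mariPOC respi and the novel RPA-based test will be calculated", with PCR as the comparator. The section closes with a general convention of 95% CIs and a P "value of <.05 will be considered significant".

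Study Size and Power Calculation says that "we focused on the assessment of MxA levels in cases with viral CAP as compared with cases with bacterial CAP/controls". Its inputs are "A difference in MxA level of 500" µg/l as the relevant effect and "A standard deviation of 1000 and 300 was assumed in cases with viral CAP and bacterial CAP/controls, respectively".

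**The concern.** A comparison of levels asks whether two groups differ on average. Diagnostic accuracy asks how well a child's MxA value separates viral from bacterial disease. The two questions can have different answers, because a clear difference in means can coexist with wide overlap between the groups.

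The article is not merely silent here. It states an MxA analysis and a basis for the sample size, and both target a quantity other than the one in the objective. The same paragraph shows that accuracy measures were in mind, since it names them for mariPOC and the RPA test.

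The study's purpose is to help clinicians separate viral from antibiotic-requiring bacterial infection. An analysis that stops at a difference in levels would leave that question unanswered. If a cutoff were then picked from the same data without a stated rule, sensitivity and specificity would tend to look too good.

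**Working it through.** **Inputs from Study Size and Power Calculation.** Difference 500 µg/l; SD 1000 (viral) and 300 (bacterial or control); two-sided alpha 0.05; power 80%; inflation 20%; 300 cases, of whom 45% are viral and 14% bacterial.

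**1. The plan's own figure.** n per group = (1000² + 300²)(1.960 + 0.842)² / 500² = 1,090,000 × 7.849 / 250,000 = 34.2, rounded up to 35. Then 35 × 1.20 = 42, as stated. Expected yield: 300 × 0.45 = 135 viral and 300 × 0.14 = 42 bacterial. The arithmetic is correct for a difference in means. At 135 versus 42, power for 500 µg/l (Welch t) is above 99%.

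**2. What 500 µg/l means for accuracy, normal model (assumption).** AUC = Φ(500 / √(1000² + 300²)) = Φ(500 / 1044) = Φ(0.479) = 0.68.

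**3. The same difference and SDs, lognormal model.** This needs a mean m for the bacterial group, which the article does not give; 100, 200 and 300 µg/l are assumed. For each group the log-scale variance is s² = ln(1 + SD²/mean²) and the log-scale mean is μ = ln(mean) − s²/2. Then AUC = Φ((μ_viral − μ_bacterial) / √(s²_viral + s²_bacterial)).

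| Bacterial mean | Viral mean | Difference in μ | Root of summed s² | AUC |
|---|---|---|---|---|
| 100 | 600 | 2.278 | 1.906 | 0.88 |
| 200 | 700 | 1.286 | 1.514 | 0.80 |
| 300 | 800 | 0.857 | 1.278 | 0.75 |

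One difference in level therefore fits AUCs from 0.68 to 0.88.

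**4. Where significance begins.** The plan allows for nonparametric testing. For a Mann-Whitney test the null SE of the AUC is √((135 + 42 + 1) / (12 × 135 × 42)) = 0.0511, so two-sided P<.05 is reached at 0.5 + 1.96 × 0.0511 = 0.60.

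**5. Precision the planned sample gives for accuracy.**
- AUC (Hanley-McNeil SE, 135 versus 42): at 0.68 the SE is 0.0436, so ±0.09 (about 0.60 to 0.77). At 0.88 the SE is 0.0249, so ±0.05.
- Specificity against bacterial CAP (Wilson 95% CI, n = 42): 66% to 89% at 80%; 71% to 93% at 85%; 77% to 96% at 90%.
- Sensitivity in viral cases (Wilson 95% CI, n = 135): 78% to 90% at 85%.

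**The case against.** **A condensed article.** A full protocol or SAP may exist, and details such as ROC method, cutoff and type of CI normally belong there. Nothing in the article says that the comparison of levels is the only MxA analysis. The ingredients for an accuracy analysis are in place: a quantitative assay and a reference algorithm fixed in advance, with a stricter variant. This stands as a limit on the claim. It does not remove it, because the MxA analysis and the sample size that the article does state are aimed elsewhere, and an analysis added in another document would not change the published basis for the sample size.

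**The rank test is close to accuracy.** The Mann-Whitney statistic divided by the product of the group sizes is the empirical AUC. That is true and makes the remedy easy, but the article promises neither that test nor the AUC as an estimate.

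**The normal model is a poor fit.** MxA cannot be negative. At the assumed bacterial means of 100 to 300 µg/l, a normal model puts 16% to 37% of bacterial cases and 21% to 27% of viral cases below zero. This stands. The figure of 0.68 should be read as one end of a range and not as a forecast.

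**A tempting stronger reading.** A reader might infer that any P<.05 would be reported as meeting objective 1, even for a marker too weak to use. The article does not support that. Its P<.05 is a general convention alongside 95% CIs, no success rule is set for objective 1, and the plan names 500 µg/l as the relevant difference, which is a stricter standard than significance alone.

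**Conclusion.** The concern holds in this form: the first objective is accuracy, while the only MxA analysis stated, and the only basis for the sample size, is a difference in levels. That difference does not settle the objective. The plan's own effect size and SDs fit an AUC anywhere from about 0.68 (normal) to 0.88 (lognormal, bacterial mean 100 µg/l), and significance on a rank test starts at about 0.60.

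The AUC range rests on the assumed distributions and on bacterial means that the article does not give. The counts of 135 and 42 rest on the plan's 45% and 14%. The conclusion that a difference in levels does not determine accuracy needs none of these assumptions. The stated 42 per group is not an arithmetic error, and the planned enrolment can support an accuracy estimate. What is missing from the stated plan is that estimate as the target, and its expected precision.

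**What to change.** **Statistical Methods.** Make the main MxA analysis the AUC with 95% CI for viral versus bacterial CAP, classified by the TREND algorithm. Add sensitivity and specificity with Wilson CIs at a cutoff fixed before the data are seen, if one is available. The only MxA cutoff in the article, 40 ng/ml, describes a commercial test and is not adopted for TREND, so a usable prior cutoff cannot be presumed. If none exists, report bootstrap or cross-validated estimates that correct for choosing the cutoff in the same data. Keep the comparison of levels as supportive.

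**Study Size and Power Calculation.** Keep 300 cases and 120 controls, and add the expected precision: AUC 95% CI of about ±0.05 to ±0.09 for AUCs of 0.88 to 0.68, and about 66% to 89% for a specificity of 80% on 42 bacterial cases.

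**Cost.** Wording and routine analysis of data already planned, with no extra children or samples. The drawback is presentational: an interval some 23 points wide for specificity looks less favourable than 80% power for a difference in levels.

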### Ethics Approval and Consent to Participate

The study will be conducted in accordance with the latest version of The Declaration of Helsinki and the fundamental principles of respect for the individual’s (Article 8) right to self-determination and to make informed decisions (Articles 20, 21, and 22) regarding participation in research, both initially and during the course of the research.

We estimate that the benefit of knowing more about viral respiratory infections with the aim of improving diagnostics of CAP overweighs the discomfort for the individual study participant in terms of extra sampling. For all the participating children, a minimal, reduced amount of blood will be collected, and accordingly, the analysis of PCT and CRP will not routinely be performed in control children for the following reasons: (1) data on these biomarkers in the controls are not necessary for the study objectives; (2) to get a sufficient amount of blood for running these analyses, it would require a larger lancet and/or additional punctures; and (3) these children would likely not have been subject to capillary puncture, were they not enrolled in the study. Results from point-of-care tests will be provided to guardians and treating physicians. Other test results will not be provided as they will be analyzed in batches and thus not influence management. Written informed consents will be collected from the guardian(s) by the study nurse/physician before sampling. To ensure confidentiality for the participants, samples will be given a study ID and results will only be presented at a group level. Data of personal identities will be stored in a password-protected data file at Sachs’ Children and Youth Hospital and will only be available to the study researchers. Good clinical practice and good laboratory practice will be followed. The study was approved by the Regional Ethical Review Board in Stockholm (ref 2017/958-31).

## Results

The study was approved by the Regional Ethical Review Board in Stockholm in June 2017 (ref 2017/958-31). A pilot study was performed from June to August 2017 to evaluate the study protocol from a logistical and methodological point of view. Overall, 6 out of 9 invited cases and 1 out of 3 invited controls were included. Valuable information was retrieved during the pilot study, which has led to alterations and improvements in the recruitment process, the questionnaire, and other study documents as well in the logistics and handling process of the samples. Enrollment of study subjects started in November 2017. Results are expected by the end of 2019.

## Discussion

### Principal Findings

The TREND study aims to improve the differential diagnosis of bacterial and viral etiology in children aged below 5 years with clinical CAP presenting at an emergency unit in a tertiary pediatric hospital in Sweden. This is the first study of children with clinical CAP that evaluates the diagnostic accuracy of MxA as a biomarker for viral CAP. Previous studies on MxA have shown promising results on the role of MxA as a biomarker for viral infection but have been smaller in size [14] or have included more heterogeneous groups of study subjects [13,15,16]. The TREND study aims to add further information on the role of MxA as a marker to improve the interpretation of viral PCR positivity and to differentiate between viral and bacterial infections with a specific focus on children with CAP. Further aims are to validate the findings from recent pediatric CAP etiology studies, including the EPIC and PERCH studies, as well as to assess the long-term complications of pediatric CAP [21-24].

### A New Algorithm for Classification of Etiology in Pediatric Community-Acquired Pneumonia Studies

One major weakness in the studies of diagnostic biomarkers in pediatric infectious diseases is the lack of a reliable gold standard for the microbiological diagnosis [5,49]. The gold standard for assigning bacterial etiology has traditionally been the detection of bacteria in cultures from normally sterile sites (lung, blood, and pleura). However, as sampling from the lung/pleura is infeasible in most cases and blood cultures have limited sensitivity, this approach is of little use in clinical studies of CAP [5]. Previous studies assessing the performance of diagnostic tests in terms of distinguishing bacterial infections from viral infections have used either an independent expert panel or a laboratory-/radiological-based approach to classify disease etiology [12-15]. Both approaches have their advantages and limitations. Using a strict microbiologically confirmed diagnosis as the reference has the advantage of high specificity, but the generalizability of the findings is hampered as the majority of children in clinical practice will not have a clear microbiologically confirmed diagnosis. In addition, for a diagnostic test to be useful, it is more important to distinguish between etiologically less clear cases of respiratory infections rather than to identify the school book examples of bacterial and viral infections. In the TREND study, we chose a more pragmatic approach favoring generalizability for microbiological accuracy. However, given that doctors in expert panels rely on microbiological and biochemical findings, we reasoned that it still would be more stringent to create an algorithm for the classification of etiology. In the TREND study, a diagnostic algorithm has been created a priori to serve as the reference based on the current evidence for the classification of CAP etiology. Detection of RSV, hMPV, influenza virus, and PIV has, in previous case-control studies, been highly associated with CAP. Furthermore, these viruses appear to be rarely detected in asymptomatic individuals, and hence, detection will be considered to be a definitive indicator of etiology [21,22,47,50,51]. For other respiratory viruses as well as for the atypical bacteria *M pneumoniae*, the clinical significance of PCR positivity is less clear owing to frequent detections in asymptomatic children [17,52-55]. For that reason, PCR positivity will not be considered enough for establishing etiology. Virkki et al reported that a CRP level of more than 80 in children aged less than or equal to 2 years and more than 120 in children aged 2 to 5 years was specific (>85%) for bacterial etiology, whereas a CRP level of less than 20 was specific for viral etiology (78%) [56]. These cutoffs will be used to aid in the definition of probable bacterial and viral infections in less clear cases. Hence, detection of viruses other than influenza, RSV, hMPV, and PIV will be considered as viral infections only if the CRP value is less than 20. Given that adenovirus has been associated with high CRP, this rule will not be applicable for adenovirus [11]. However, adenovirus detections will not be considered in the strict algorithm, as asymptomatic detection of the virus is common [17]. Finally, given that CRP levels depend on the disease duration and to avoid false-negative test results (ie, low but rising CRP values), an additional criterion of reported fever duration of more than 24 hours will be applied in the TREND study when considering CRP levels [45]. As discussed above, there is no optimal reference standard for the classification of CAP etiology, neither clinically nor in research. However, we believe that much is to be gained if we use an algorithm instead of an expert panel. The decisions taken by expert panels differ between different studies, over time, and between different settings. When using an algorithm, this can be controlled for. We look forward to comments and inputs on our algorithm so that together we can develop it further.

### Difficulties in Pediatric Community-Acquired Pneumonia Etiology Studies

The WHO criteria for clinical CAP lack specificity and will result in the inclusion of a significant proportion of children who will not have true CAP, including children with bronchiolitis and asthma [57]. To improve the specificity of the WHO criteria for clinical CAP, a rapid-acting bronchodilator will be administered to children with wheezing and chest indrawing, as suggested by the PERCH study team [43]. Other clinical parameters from the PERCH study will also be included and used for further subanalyses [43].

Conducting research in the pediatric emergency department is difficult [58]. High patient flows and long waiting times create a stressful environment for all personnel categories. Motivating nurses/doctors to spend the extra time and effort it takes to recruit patients is, therefore, challenging. Continuous education/information about the research project, interpersonnel teamwork (nurse and doctor), and incentives are all key success factors. Recruitment of healthy controls in this age group is an obvious challenge as the sampling (blood and nasopharyngeal sampling) causes discomfort to the child. Therefore, attempts have been made to include patients who will undergo elective hand surgery (and thereby be sedated during the sampling). Certain clinical parameters can be deceptive if not recorded correctly, which is a potential source of bias. In children where peripheral oxygen saturation and heart rate are measured continuously, data will still only be recorded at certain time points when the children are at rest.

### Requirements of Future Rapid Diagnostic Tests

Transcriptomic studies have shown promise in differentiation between different infectious agents but currently require advanced instrumentation with a long turnaround time and are hence more suitable for an intensive care unit setting than for routine testing at pediatric emergency units [59]. However, given the complexity of the host immune response elicited by respiratory pathogens, it is possible that a single biomarker will not be sufficient to accurately differentiate between viral and bacterial CAP. However, MxA could be valuable in a rapid combination test of biomarkers and selected microbiological testing if it proves to be specific for viral CAP. Such commercial combination point-of-care tests of inflammatory biomarkers are already being developed and some, such as FebriDx and MeMed BV, have shown promise [15,60].

Improved near-patient differential diagnosis is a prerequisite for rational antibiotic use and decreasing unnecessary antibiotic treatment. Furthermore, easier identification of the pathogens causing acute respiratory infections makes it easier to advise guardians to care for their sick children and for better disease surveillance in the society. Hence, the findings from the TREND project can be an important step toward the improved care of children with clinical CAP. At this stage, the methods are developed and evaluated in a Swedish context but might have wider implications, for example, to resource-limited settings where the need for similar tests is even higher than in a high-income context such as Sweden.

